## Abstract

**Introduction**: Population aging is a growing and challenging phenomenon, primarily due to its association with functional decline and sarcopenia, which increase the risk of falls. These events have significant impacts on public health and the quality of life of older adults. Regular physical activity has shown benefits in reducing falls and their consequences, with systemic vibratory therapy (SVT) emerging as a promising strategy to mitigate these adverse outcomes. However, evidence on the actual effectiveness of this therapeutic approach remains limited, as does clarity regarding optimal body position, protocol parameters, and equipment when combined with physical activity programs. **Objectives**: To compare the effect of systemic vibratory therapy (SVT) associated with a physical activity program on the perception of fear of falling in older adults (M01.060.116.100). As secondary outcomes, the study will assess functional physical conditioning, electromyographic activity, muscular synergy, and center of pressure oscillation in this population. **Methods**: A randomized controlled clinical trial with blinded outcome assessors and blinded statistical analysis will be conducted with 192 older adults participating in the UNATI/UNISUAM program. Participants will be allocated into three groups: (A) usual physical activity; (B) usual physical activity + SVT in a semi-squat position; and (C) usual physical activity + SVT in a seated position. Assessments will include sociodemographic data, concern about falling assessed using the Falls Efficacy Scale-International (FES-I), physical performance (2 min stationary march test), surface electromyography of the tibialis anterior and medial gastrocnemius muscles, along with posturography using a force platform. **Results**: This study will provide information on outcomes related to fall risk, balance, physical fitness, and neuromuscular variables in older adults undergoing two distinct SVT protocols. **Clinical Trials Registration**: Brazilian Registry of Clinical Trials RBR-68pry5j. Registered on 8 December 2025.

## 1. Introduction

Population aging is a growing global phenomenon, especially in developing countries such as Brazil [1]. According to the World Health Organization (WHO) [1], individuals aged 60 or over are considered elderly in countries like Brazil. Projections from the Brazilian Institute of Geography and Statistics (IBGE) indicate a significant increase in the proportion of elderly individuals by 2050 [2,3].

As aging progresses, several physiological changes become evident, including loss of muscle mass and strength, reduced reflexes and motor reaction time, sensory and cognitive decline, as well as hormonal and metabolic alterations [4]. These factors contribute to an increased risk of falls, which place a substantial burden on the healthcare system, including prolonged hospitalizations, loss of autonomy, and reduced quality of life among older adults [5,6]. The WHO estimates that around 37.3 million severe falls occur globally each year, resulting in approximately 684,000 deaths (https://www.who.int/news-room/fact-sheets/detail/falls. Accessed on 31 December 2025). In Brazil alone, over 1.7 million hospitalizations due to falls among the elderly were recorded between 2000 and 2020, particularly among women aged over 80 years in the Southeast region [5]. Fractures were the main complications, mostly affecting the lower limbs, followed by upper limbs and the spine, with 60% of falls occurring at home [7].

In this context, promoting physical activity among older adults is essential. Physical activity provides numerous benefits, including reduced muscle loss, improved autonomy, increased social interaction, enhanced functional independence, and reduced risk of age-related diseases [8,9,10]. Moreover, it serves as an effective non-pharmacological strategy for fall prevention. Physical activity refers to any bodily movement that results in energy expenditure, while physical exercise is a planned and structured activity [9]. In this regard, the WHO advocates for the concept of active aging, which emphasizes the promotion of autonomy, functional independence, social participation, and healthy life expectancy [11].

A promising intervention is systemic vibratory therapy (SVT), which uses vibration platforms to provide mechanical stimuli capable of eliciting muscular, proprioceptive, and hormonal responses [12,13]. Reduced muscle strength, impaired sensory integration, and altered postural adjustments in older adults are associated with an increased risk of falls [11]. Previous studies suggest that SVT may improve lower limb muscle performance, balance, mobility, and physical function in older populations, although the magnitude of these effects appears to depend on protocol characteristics such as frequency (F), peak-to-peak displacement (D), exposure time, rest intervals, and body position during vibration exposure [13,14]. Despite these potential benefits, the ideal SVT protocol for older adults is not yet defined. Current evidence still shows considerable heterogeneity regarding vibration parameters, intervention duration, equipment characteristics, and participant positioning, which limits the establishment of standardized recommendations for clinical practice [12]. Body position during SVT can be particularly relevant, as it can modify axial load, lower limb muscle activation, postural demand, comfort, and safety. The semi-squat position can increase active lower limb engagement and proprioceptive stimulation, while the seated position can reduce weight-bearing demands and provide a more tolerable alternative for frail, sedentary, or low-functional older adults [13,14,15]. Therefore, comparing these positions can help clarify whether the effects of SVT are primarily related to exposure to mechanical vibration itself or to the combination of vibration with active postural and muscular demands.

Beyond objective fall risk metrics, concern about falling is a patient-centered outcome that can constrain activity participation and undermine adherence to exercise-based prevention strategies. Conceptually, falls efficacy reflects an older adult’s perceived capability to prevent and manage falls in daily life; thus, quantifying change in this construct provides clinically relevant information that complements performance- and physiology-based outcomes [16,17]. The Falls Efficacy Scale-International (FES-I) is among the most widely used instruments to assess concerns about falling, and recent syntheses support its measurement properties and interpretability for older populations, although responsiveness benchmarks may vary across settings [18]. Accordingly, the present trial defines change in FES-I from baseline to post-intervention as the primary endpoint, while physical conditioning, neuromuscular activity, and postural control outcomes are retained as secondary measures to help contextualize potential physiological pathways of systemic vibratory therapy combined with habitual physical activity. Thus, this study aims to compare the effects of SVT associated with a physical activity program on fall concern in older adults. As secondary outcomes, the study will assess functional physical fitness, electromyographic activity, muscle synergy, and center of pressure oscillation [12,13,14,15].

Our hypothesis is that SVT combined with habitual physical activity will produce greater improvements in concern about falling, functional fitness, postural control, and neuromuscular variables compared with habitual physical activity alone. We also hypothesize that the semi-squat and seated SVT positions may produce different neuromuscular responses due to differences in axial load, lower limb muscle activation, and postural demand.

## 2. Materials and Methods

### 2.1. Study Design

This study is a randomized controlled clinical trial with blinded outcome assessors and blinded statistical analysis. Due to the perceptible nature of the vibration stimulus and the absence of a sham-vibration condition, participant blinding cannot be fully guaranteed. Therefore, blinding procedures will focus on maintaining the outcome assessors and the researchers responsible for statistical analysis unaware of group allocation throughout the trial. The study will adhere to the recommendations of the CONSORT 2025 statement [19]. The primary aim is to investigate the effects of SVT combined with a physical activity program on the concern about falling, functional physical conditioning, and neuromuscular variables in older adults.

A total of 192 older adults enrolled in the Open University for the Elderly (UNATI) at Centro Universitário Augusto Motta (UNISUAM), Bonsucesso Unit, will be recruited. Participants will be allocated in a 1:1:1 ratio into three groups using sequentially numbered, opaque, sealed envelopes prepared from a computer-generated randomization list. The allocation sequence will be implemented after completion of baseline assessments to preserve allocation concealment. In the control group (Group A), participants will be considered a usual physical activity control group. Participants allocated to this group will continue their regular activities offered by the UNATI/UNISUAM program, including light walking, stretching exercises, activities of daily living, and recreational cognitive activities. No additional vibration stimulus or sham-vibration procedure will be applied. Therefore, the study will compare systemic vibratory therapy combined with habitual physical activity in two distinct positions versus habitual physical activity alone. In the semi-squat intervention group (Group B), participants will engage in the same routine activities and, 30 min after the end of their UNATI sessions, will be directed to the Laboratory of Musculoskeletal Performance of the Graduate Program in Rehabilitation Sciences (PPGCR/UNISUAM), where SVT will be performed in a semi-squat position with knees flexed at 120°. To ensure positioning consistency, the platform base will be pre-marked to standardize foot placement. The intervention will use mechanical vibration at F of 15, 20, and 25 Hz with a D of 5 mm, corresponding to peak accelerations (Apeak) of 2.3 g, 4.1 g, and 6.4 g. Each frequency will be applied for 1 min, with a 1 min rest interval between frequencies, in a cycle repeated three times, totaling 18 min per session. Interventions will occur twice weekly, for a total of 10 sessions. All sessions will be conducted by a research assistant trained in the operation of the vibration platform. Systemic vibratory therapy will be delivered using a Kikos P204IXC alternating oscillatory vibration platform (manufacturer is Kikos) manufactured in São Paulo, Brazil.

The seated intervention group (Group C) will follow the same routine of physical activities and undergo SVT in a seated position on a 30 cm high chair, with knees flexed at 120° and hands resting on the thighs in a comfortable posture, simulating the joint angles of the semi-squat protocol. The vibration parameters will be the same as those used for Group B.

Initial assessments will be conducted before randomization and before the start of the intervention period. Post-intervention assessments will be conducted within 48 h after the last intervention session, preferably at the same time as the initial assessment, in order to minimize possible circadian variations and effects related to fatigue. The same sequence of assessments will be maintained for all participants: (1) the Falls Efficacy Scale-International (FES-I, Brazilian version) to assess concern about falling; (2) the 2 min stationary march test to assess functional physical fitness; (3) bilateral surface electromyography (sEMG) of the tibialis anterior and medial gastrocnemius muscles using the EMG832C system (EMG System do Brasil, São Paulo, Brazil); and (4) posturography performed simultaneously with sEMG using a force platform (AccuSway PLUS, AMTI, Watertown, MA, USA).

### 2.2. Registry

This trial was approved by the Research Ethics Committee of the Augusto Motta University Center UNISUAM (IRB No. 7.782.752 on 21 August 2025), according to the guidelines of Law No. 14.874/24 of the National Health Council, in accordance with the Helsinki Declaration for research in humans, and prospectively registered in the Brazilian Registry of Clinical Trials (registration code: RBR-68pry5j, registration dated: 8 December 2025, WHO Universal Trial Number: U1111-1332-5737, available at https://ensaiosclinicos.gov.br/rg/RBR-68pry5j (accessed on 31 December 2025)).

### 2.3. Setting

The trial will be conducted at the Musculoskeletal Performance Laboratory of the Graduate Program in Rehabilitation Science (PPGCR/UNISUAM), Rio de Janeiro, Brazil.

### 2.4. Recruitment

The sample will be recruited intentionally and by convenience and opportunity at the Open University for Seniors (UNATI) of the Augusto Motta University Center (UNISUAM). Although participants are recruited from the UNATI/UNISUAM program, the research procedures will always be conducted by a research team independent of the regular UNATI team, as well as those responsible for routine activities.

Baseline characteristics will include sociodemographic data, history of falls, and level of physical activity. Previous falls will be recorded based on the FES-I and self-report over the past 12 months. Physical activity level will be assessed at baseline using the International Physical Activity Questionnaire (IPAQ) [20]. These variables will be described by group and considered in the interpretation of baseline comparability and potential confounding factors.

The UNATI team will not participate in randomization, allocation concealment, outcome assessment, intervention application, or statistical analysis. To minimize cross-contamination between groups, intervention sessions will be scheduled separately, and participants will be instructed not to share details of the procedures to which they were allocated with other participants during the study period. The study will be conducted at the Musculoskeletal Performance Laboratory, linked to the Postgraduate Program in Rehabilitation Sciences (PPGCR/UNISUAM), located at [name].

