### 2.16. Statistical Analysis

Sample size calculation

An a priori sample size calculation was performed using G*Power software (v. 3.1.9.6) [28]. A conservative medium omnibus effect size (Cohen’s f = 0.25) was adopted, consistent with methodological guidance for a priori estimation in strength and conditioning/exercise research [29]. Assuming α = 0.05, power (1 − β) = 0.80, and three parallel groups, the required total sample size for an omnibus ANOVA comparison is 159 participants (53 per group). To account for potential losses to follow-up of up to 20%, the planned recruitment target was increased to 192 participants (64 per group), ensuring adequate power for the primary analyses. Participants of both sexes, over 60 years of age (M01.060.116.100), participating in the Open University for the Elderly program at Augusto Motta University (UNATI/UNISUAM), will be included.

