### 2.17. Data Analysis

Descriptive statistics will be presented as mean ± standard deviation for continuous variables and as frequency (percentage) for categorical variables. Distributional assumptions will be evaluated using Shapiro–Wilk tests and visual inspection (histograms and Q–Q plots), and homogeneity of variance will be examined (e.g., Bartlett/Levene, as appropriate). Because the trial includes three groups and two time points (baseline and post-intervention), the primary inferential objective for each outcome will be to test the Group × Time interaction, which directly evaluates whether pre–post changes differ between groups.

For outcomes meeting parametric assumptions, a mixed-design model will be applied with Group (A, B, C) as a between-subject factor and Time (baseline, post-intervention) as a within-subject factor. The main effect of Group, main effect of Time, and, critically, the Group × Time interaction will be reported. Because Time has only two levels, sphericity is not applicable. If the interaction is statistically significant, planned follow-up comparisons (simple effects) will be conducted to compare: (i) pre–post change within each group and/or (ii) between-group differences at each time point, using multiplicity-adjusted procedures (see below).

If parametric assumptions are violated, outcomes will be analyzed using an appropriate robust repeated-measures approach (e.g., transformation where suitable, or mixed-model estimation with robust standard errors), preserving the Group × Time framework. In all cases, inference will be centered on the interaction term as the test consistent with the study design.

Multiplicity control: The primary outcome (FES-I) will be tested at α = 0.05 (two-sided). Secondary outcomes will be interpreted as supportive/exploratory and will include multiplicity control to reduce false-positive risk across the outcome family. For post hoc/simple-effects contrasts following a significant interaction, *p*-values will be adjusted (e.g., Holm–Bonferroni). For multiple secondary outcomes, an additional correction strategy will be applied (e.g., false discovery rate control) to maintain interpretability across the secondary endpoint set.

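### Baseline variables already collected serve only to interpret comparability and confounding; a short pre-specified covariate list in the FES-I model could add modest precision and would close the open wording

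*Protocol article*

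**What the plan says.** Section 2.4 of the protocol article (Recruitment) lists the baseline characteristics as sociodemographic data, falls history and physical activity level. Activity is measured with the IPAQ, and falls cover the previous 12 months. Age and sex are not named there but are implied by sociodemographic data; section 2.12 uses both to classify the march test. The section gives these variables one use: "These variables will be described by group and considered in the interpretation of baseline comparability and potential confounding factors".

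Section 2.17 (Data Analysis) states the primary model: "a mixed-design model will be applied with Group (A, B, C) as a between-subject factor and Time (baseline, post-intervention) as a within-subject factor". Inference rests on the Group × Time interaction. No covariate is named, apart from baseline FES-I, which enters as the first level of Time.

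On allocation, section 2.1 says: "Participants will be allocated in a 1:1:1 ratio into three groups". Sections 2.1 and 2.6 describe a computer-generated list and sequentially numbered, opaque, sealed envelopes opened after the baseline assessments. No stratification factor is named.

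**The concern.** There are two small problems.

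1. **Wording.** With concealed random allocation, any baseline difference between arms is due to chance, and the standard error of the planned test already allows for it. Calling such differences potential confounding, with no rule for what follows, leaves the reading of the FES-I result open to the observed baseline table.
2. **Precision.** Variables that predict FES-I change can reduce residual variance if they enter the model by a rule set in advance. Description and interpretation alone cannot do this. The data will be collected anyway, so the plan gives up a possible gain at almost no saving.

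At stake are a few points of power at most and a cleaner interpretation. The validity of the primary test is not in question.

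**Working it through.** **Inputs from the document (section 2.16).** "Assuming α = 0.05, power (1 − β) = 0.80, and three parallel groups"; "A conservative medium omnibus effect size (Cohen’s f = 0.25) was adopted"; required N of 159, or 53 per group; recruitment target 192 for losses of up to 20%. The document gives no R² for any covariate, so R² is assumed below. I take f = 0.25 to apply on the scale actually tested, the pre–post change.

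**Step 1: reproduce the stated N.** For a one-way omnibus F test with three groups, λ = N·f² with degrees of freedom 2 and N − 3.
- At N = 159, λ = 159 × 0.0625 = 9.94 and power is 80.5%.
- The smallest N reaching 80% is 158 (80.2%). Rounding up to equal groups gives 159, so the stated figure reproduces.

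**Step 2: size of chance imbalance at 53 per arm.**
- For a standardised covariate, the SD of the difference between two arms is √(2/53) = 0.19.
- For falls history at an assumed prevalence of 30%, it is √(2 × 0.3 × 0.7/53) = 0.089, or 8.9 percentage points.

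Visible differences are therefore to be expected and are no sign of confounding.

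**Step 3: gain from pre-specified adjustment.** If the covariates explain a share R² of the change variance, f becomes 0.25/√(1 − R²). The standard error falls by 1 − √(1 − R²), and the equivalent number of extra participants is 159/(1 − R²) − 159. Four error degrees of freedom are charged for the covariates.

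| Assumed R² | Adjusted f | SE reduction | Equivalent extra participants | Power at N = 159 | Power at N = 153 |
|---|---|---|---|---|---|
| unadjusted | 0.250 | – | – | 80.5% | 78.8% |
| 0 | 0.250 | 0 | 0 | 80.5% | 78.8% |
| 0.02 | 0.2525 | 1.0% | 3.2 | 81.3% | 79.7% |
| 0.05 | 0.2565 | 2.5% | 8.4 | 82.6% | 81.0% |
| 0.10 | 0.2635 | 5.1% | 17.7 | 84.7% | 83.1% |

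The N = 153 column is what remains of 192 after the stated 20% loss (192 × 0.8 = 153.6). At R² = 0 and N = 159, power goes from 80.49% to 80.47%, so the cost is about 0.02 points. Using five degrees of freedom, as a three-category IPAQ would need, gives 80.46%.

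**Step 4: how the covariates must enter.** With complete data and two time points, the interaction test is a test on change scores, and a covariate main effect common to both times cancels out of the change. One simulated data set with generic (not trial) figures shows this.
- Group × Time estimates of −0.01311 and −0.20871, each with SE 0.17069, were identical with and without main-effect covariates.
- Adding covariate × Time terms changed them to −0.01935 and −0.21510, with SEs of 0.17217 and 0.17129.

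Only the second form adjusts the test. The slightly larger standard errors there show that a gain is not guaranteed when the covariates barely predict change.

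**Step 5: validity of the planned test.** In 3,000 simulated null trials, the unadjusted test rejected in about 5.5% and the pre-specified adjusted test in 5.1%. Both are within simulation error of 5%.

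**The case against.** The strongest reply is that nothing here is wrong. The unadjusted randomised comparison is valid, section 2.17 fixes the model and centres inference on the interaction, and section 2.1 keeps the analysts unaware of allocation. Describing baseline characteristics by group is ordinary reporting. All of this stands, and it is why the point is minor.

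A reader might infer that the investigators will judge imbalance by eye and then add covariates, or explain a result away. The document does not say so. It speaks of description and interpretation, and nowhere provides for selecting covariates after the data are seen. Choosing the smallest p-value over all 16 subsets of four covariates would raise the type I error to 8.4%, 9.4% or 11.5% at assumed R² of 0.05, 0.10 or 0.20. That is a worst case the protocol does not propose, so those figures are not evidence against this plan.

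The second reply is that the gain is speculative. Variables that predict the level of concern about falling need not predict its change, because each participant's stable level is already differenced out. This also stands: R² for change is unknown, and the benefit could be nil.

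The third reply is that a covariate list may sit in a full protocol or SAP that is not shown. The absence of such a list is therefore not the complaint. The complaint is that section 2.4 states a use for these variables, as possible confounders to be weighed in interpretation, and that this use suits a randomised trial poorly.

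Finally, section 2.4 says previous falls are recorded from both the FES-I and self-report, while section 2.11 describes the FES-I as 16 ratings of concern, with no count of falls. A falls covariate needs a source separate from the outcome instrument. The objection is sound, and the fix below deals with it.

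**Conclusion.** The point holds as a low-severity improvement. The planned unadjusted Group × Time test of FES-I is valid and keeps its error rate. What the plan forgoes is a possible gain of about 1 to 4 power points at N = 159 (80.5% to between 81.3% and 84.7%), on the assumption that the covariates explain 2% to 10% of change variance. If they explain none, there is essentially no gain or loss. The reference to potential confounding also leaves interpretation open to chance differences in the baseline table. The documents do not support a claim of bias, of an inflated type I error, or of planned post hoc covariate selection. The figures rest on the assumed R² values, on f = 0.25 applying to change, and on four covariate degrees of freedom.

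**What to change.** Before unblinding, state in section 2.17:

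> The primary FES-I model includes age, sex, falls in the past 12 months (from self-report only, not from the FES-I) and IPAQ level, each with its interaction with Time, whatever baseline imbalance is observed. No further baseline variables are added after unblinding. The unadjusted Group × Time result is reported alongside.

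An acceptable alternative is to enter the same covariates in an ANCOVA of post-intervention FES-I adjusted for baseline FES-I. Main effects alone in the Group × Time model would not do, for the reason shown in the working.

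In section 2.4, delete the reference to potential confounding and keep the descriptive baseline table. Also state there that the falls history comes from self-report.

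The cost is a few sentences and four or five degrees of freedom, with no new data. The gain depends on an R² that is not known in advance.
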